**3.2 Frequency-Based Outcomes**

Frequency-based outcomes, such as caregiver-perpetrated violence, will be analyzed using either Poisson or negative binomial regression models. The choice of model will be determined by the presence of overdispersion in the data.

- **Model Specification:** The model structure will be identical to that described in section 3.1, including random and fixed effects.

**3.3 Sensitivity Analyses**

To assess the robustness of the findings, sensitivity analyses will be conducted by adjusting the primary models for a set of pre-specified covariates.

- **Covariates:** Child age, child gender, caregiver age, and caregiver gender.

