**2. Sample Size and Power Calculation**

As this is a pragmatic trial, the sample size is primarily determined by real-world logistical constraints. While initial estimates suggested access to approximately 79 participants per group, the decision to further embed the intervention into the routine parenting support offered by the preschool allowed us to access all families within the setting.

To maximize the available sample, based on recruitment capacity, power calculations will assume 21 clusters, each comprising 20–35 participants (four discrete values), and intra-cluster correlation coefficients (ICCs) ranging from 0.01 to 0.05 (five values).

Prior to implementation, power calculations will be conducted to estimate the minimum detectable effect size (MDES) for the primary outcome, for opportunities for early learning and stimulation and caregiver-perpetrated violence, under fixed sample size constraints. MDES estimates will be based on a multilevel Poisson/negative binomial and a linear regression framework.

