**3. Intervention Effect Estimation**

The primary evaluation of intervention effects will be conducted at the post-intervention timepoint (T1).

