**3.1 Continuous Outcomes**

Continuous outcomes will be analyzed using multilevel linear regression models.

- **Model Specification:**
  - **Random Effects:** Participant ID nested within cluster.
  - **Fixed Effects:** Group (intervention vs. control), time (T0, T1, T2, T3), and the group × time interaction term. The intervention effect will be determined by the interaction term.

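### Adjusting the group × time models for demographic covariates is a weak robustness check: as main effects they leave the linear and Poisson estimates unchanged when data are complete

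*SAP*

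**What the plan says.** Section 3.1 of the SAP fits a multilevel linear model with group, time and their product, and random effects given as "Participant ID nested within cluster". The effect is defined there: "The intervention effect will be determined by the interaction term". Section 3.2 carries this over to count outcomes, fitted as Poisson or negative binomial: "The model structure will be identical to that described in section 3.1, including random and fixed effects". Section 3 makes T1 the primary evaluation.

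Section 3.3 is the only analysis labelled a sensitivity analysis. Its purpose is "To assess the robustness of the findings", and its method is that "sensitivity analyses will be conducted by adjusting the primary models for a set of pre-specified covariates". The covariates are "Child age, child gender, caregiver age, and caregiver gender". The section does not say whether they enter only as main effects or also by time, nor whether the ages are baseline values. It varies no assumption about missing data or model form.

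**The concern.** The four covariates are properties of the participant. Gender does not change, and age is either a baseline value or advances with the calendar. The treatment effect is a difference between arms in change from T0. A variable that adds the same amount to a participant's outcome at every wave drops out of that change.

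The adjusted and unadjusted results may therefore agree because of how the model is built, not because the finding is robust. A report could say that results were robust to adjustment for age and gender when the check had little chance of showing otherwise. Section 2 assumes 21 clusters. If assignment was by cluster (this SAP does not say), chance imbalance in such variables is plausible.

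**Working it through.** The SAP states no figure on this point, so the check is algebra followed by simulation.

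**Linear model, complete data.** For participant i in cluster j at time t (0 or 1), with arm g and baseline covariate x:

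y = b0 + b1·g + b2·t + b3·g·t + c·x + u_j + v_i + e_t

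The change is y_1 − y_0 = b2 + b3·g + (e_1 − e_0). The term c·x and both random intercepts cancel. The participant's sum across waves carries c·x, but b1 is free there, so the sum adds nothing about b3. The estimate of b3 is the difference between arms in mean change, whatever c is. With four waves the same holds for each within-participant contrast.

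**Poisson model, complete data.** Given a participant's total count, the share falling at T1 is exp(b2 + b3·g) / [1 + exp(b2 + b3·g)]. Neither x nor the random intercept appears, so b3 again comes from the within-participant part.

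**Negative binomial.** This factorisation fails, so exact equality is not expected.

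**Simulation inputs.** From section 2: 21 clusters, 20 participants each (the low end of the range) and ICC 0.05 (the high end). Covariate effects, imbalance and dropout are assumptions. Linear models had cluster and participant intercepts. Count models had a participant intercept only, 500 participants and two times; their standard errors were unreliable, so only shifts in the estimate are used.

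**Shift in the T1 group × time estimate after adding covariate main effects:**

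| Setting | Shift | In SE |
|---|---|---|
| Linear, complete | 0.0000 in every dataset | 0 |
| Poisson, complete | 0.0000 in 4 of 4 | – |
| Negative binomial, complete (log scale) | -0.005 to -0.071 | – |
| Linear, 5–20% dropout per wave unrelated to covariates | at most 0.02 in size | under 0.2 |
| Linear, 10–20% per wave, mildly covariate-related and differing by arm | 0.005 to 0.054 | about 0.05 to 0.5 |
| Linear, 20% per wave, strongly so | 0.03 to 0.12 | about 0.3 to 1.1 |
| Linear, most extreme case (about 35% of records lost) | 0.12 to 0.16 | about 1.0 to 1.4 |
| Poisson, strong differential dropout (log scale) | 0.05 to 0.08 | – |
| Negative binomial, strong differential dropout (log scale) | 0.10 to 0.17 | – |

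**What the check can miss.** Linear model, complete data, simulated effect -0.3, covariate imbalance 0.5 SD, covariate effect on change 0.3. The expected bias is 0.5 × 0.3 = 0.15, so the unadjusted estimate should centre on -0.3 + 0.15 = -0.15.

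| Dataset | Unadjusted (SE) | Main effects added (SE) | Covariate × time added (SE) |
|---|---|---|---|
| 1 | -0.188 (0.1005) | -0.188 (0.1005) | -0.393 (0.1046) |
| 2 | -0.099 (0.0990) | -0.099 (0.0990) | -0.321 (0.1009) |
| 3 | -0.173 (0.1011) | -0.173 (0.1011) | -0.279 (0.1003) |

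The first two columns of estimates average (-0.188 - 0.099 - 0.173) / 3 = -0.153. The third averages (-0.393 - 0.321 - 0.279) / 3 = -0.331.

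**The case against.** A reader might infer that the adjusted analysis can never move the effect and will report robustness whatever the data show. The documents do not support that. Section 3.2 allows a negative binomial model, which does move with complete data, and nothing in the SAP guarantees complete data. Covariate-related dropout that differs by arm can shift the linear estimate by a sizeable part of a standard error, or by more than one in extreme cases. So the analysis has some ability to pick up covariate-related attrition.

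Four further objections deserve an answer.

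- **Level-only imbalance is already handled.** If a covariate affects only the level of the outcome, the change contrast has removed its imbalance, and an unchanged estimate is correct. This stands. In one simulated dataset with a strongly prognostic covariate imbalanced by 0.6 SD, covariate × time terms moved the estimate only from 0.24834 to 0.24963, which is 0.00129 / 0.0858 = 0.015 SE. Harm needs imbalance together with an effect on change, and the SAP gives no figure for either.
- **The SAP does not say main effects only.** True, but section 4 names an interaction explicitly when it wants one, whereas section 3.3 speaks only of adjusting. Section 7 also says that this SAP fixes its models exactly. Similarly, section 3.1 does not say random intercepts, but section 6 does for its own models. Using age at each wave changes little if assessments are simultaneous, because ageing is then absorbed by the time effects.
- **Section 4 brings in demographic status by time.** Only in part. That is a moderation analysis, its demographic status is undefined, and it gives no adjusted overall effect.
- **The primary result is untouched.** Correct. This limits the weight of the point but does not make the check informative.

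**Conclusion.** The point holds in a limited form. On the ordinary reading, the section 3.3 adjustment leaves group × time exactly unchanged in the linear and Poisson models with complete data, and within 0.2 SE in the linear model under dropout unrelated to the covariates. Any movement comes through missing data or the negative binomial form. Agreement between adjusted and unadjusted results is therefore weak evidence of robustness. It cannot reveal bias from a covariate that is both imbalanced between arms and predictive of change.

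The exact result rests on three assumptions: baseline values, main effects only and random intercepts. The size of the bias that could be missed rests on assumed values. At 0.5 SD imbalance and an effect of 0.3 on change it is 0.15, half the simulated effect. It is zero if the covariate does not predict change. The trial's primary estimate, its standard error and its test are not affected. What is at stake is the claim of robustness attached to them.

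**What to change.** Amend section 3.3 in one of two ways.

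1. Keep the group × time models, and state that each of the four covariates enters at its baseline value together with its × time interaction.
2. Run the adjusted sensitivity analysis on the T1 outcome, with the baseline outcome and the four covariates as predictors. Report it beside the same T1 model without the four covariates, so that the change of model is not confused with the adjustment.

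No new data are needed. Option 1 adds 4 interaction terms if only T0 and T1 are modelled, or 4 × 3 = 12 with four categorical waves and one-parameter covariates. Precision may fall slightly. In the three datasets tabulated above the standard error changed by +4%, +2% and -1%. In the 0.6 SD dataset it rose from 0.0858 to 0.0932, about 9%. That cost falls on a supporting analysis only.

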**4. Subgroup and Moderation Analyses**

To examine whether intervention effects differ by demographic status, moderation analyses will be conducted.

- **Model Specification:** A three-way interaction term (group × time × demographic status) will be added to the original models.

**5. Follow-up Analysis in the Intervention Group**

Due to the waitlist control design, the control group began receiving the intervention after the post-intervention (T1) assessment. Therefore, between-group comparisons at the 6-month (T2) and 12-month (T3) follow-ups are not possible.

- **Method:** Analyses will be restricted to the intervention group data.
- **Generalized linear mixed-effects models** will be applied, using baseline (T0) as the reference point.
- **Model Specification:**
  - **Random Effect:** Participant ID nested within cluster.
  - **Fixed Effect:** Time (T1, T2, T3) will be included as a fixed effect to assess changes in outcomes from baseline.

**6. Causal Effect Among Compliers**

The Complier Average Causal Effect (CACE) will be estimated using a two-stage instrumental variable (IV) approach, with random assignment serving as the instrument for compliance.

- **Stage 1:** Compliance status (defined as completing at least 30 chatbot modules) will be regressed on the randomization variable to generate predicted compliance probabilities for each participant.
- **Stage 2:** Each outcome will be modelled as a function of the predicted compliance indicator from Stage 1. This stage will use mixed-effects regression models with random intercepts at both the cluster and participant levels to account for data clustering and repeated measures.
  - Continuous outcomes will be analyzed using linear mixed-effects models.
  - Count outcomes will be analyzed using Poisson or negative binomial mixed-effects models, as appropriate.

This two-stage IV framework is designed to provide an unbiased estimate of the causal effect of the intervention among compliers, addressing non-adherence while preserving the benefits of randomization.

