**Statistical Analysis Plan**

**1. General Principles**

All primary analyses will be conducted following the Intention-to-Treat (ITT) principle. All participants will be analyzed in the groups to which they were originally assigned, regardless of the level of intervention completion or dosage received.

Unless otherwise specified, a p-value of < 0.05 will be considered statistically significant for all analyses.

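### The 30-module complier analysis is called unbiased, but this needs zero effect from 1–29 modules, which the SAP neither states nor justifies

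*SAP*

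**What the plan says.** SAP Section 6 plans a two-stage instrumental-variable estimate of the complier average causal effect (CACE), "with random assignment serving as the instrument for compliance". Compliance is a yes/no variable: "Compliance status (defined as completing at least 30 chatbot modules". In Stage 1 it "will be regressed on the randomization variable to generate predicted compliance probabilities for each participant". Stage 2 then reads: "Each outcome will be modelled as a function of the predicted compliance indicator from Stage 1". The section closes by saying that the framework is "designed to provide an unbiased estimate of the causal effect of the intervention among compliers".

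Two other places matter. Section 1 treats exposure as graded when it keeps participants in their assigned groups "regardless of the level of intervention completion or dosage received". Section 5 says that "the control group began receiving the intervention after the post-intervention (T1) assessment", so up to T1 non-compliance is one-sided if the waitlist is kept.

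Section 6 does not mention the exclusion restriction and gives no reason for a cut at 30. The sensitivity analyses in Section 3.3 add covariates only; no other cut and no dose-based analysis is planned. This cannot be left to the protocol, because Section 7 presents the SAP as the place where the CACE analysis is precisely defined.

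**The concern.** An instrumental-variable estimate identifies the complier effect only if assignment changes outcomes solely through the coded compliance variable. With a cut at 30, a participant who completes 29 modules is coded the same as one who completes none. Anything that the first 29 modules do to parenting behaviour is then a path from assignment to outcome that bypasses the compliance variable.

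Such an effect stays in the ITT difference (the numerator) while the people who had it are left out of the share of compliers (the denominator). It is credited to those with 30 or more modules. The resulting bias does not shrink as the sample grows. The trial data cannot settle the matter either, since partial users in the control group cannot be identified and partial users therefore have no randomised comparison of their own.

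At stake is how the complier effect is read. It would be taken as the gain from completing at least 30 modules, and the word *unbiased* invites readers to accept its size at face value.

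**Working it through.** **No figure to reproduce.** The SAP gives no CACE value, compliance rate, total number of modules or expected effect. All shares and effects below are assumptions.

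**Set-up (linear outcome, T1 contrast).** Let pc be the share of the intervention arm with 30 or more modules, pp the share with 1–29, and dc and dp their mean effects. Assume no effect at zero modules and no control access before T1.

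- ITT = pc·dc + pp·dp
- Stage 1 contains randomisation only, so predicted compliance takes one value per arm. The linear two-stage estimate of the T1 contrast is then ITT / pc.
- Planned estimate = dc + (pp/pc)·dp
- Factor = planned estimate / dc = 1 + (pp/pc)·(dp/dc)

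**Size under assumed inputs**

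| pc | pp | dp/dc | Arithmetic | Factor |
|---|---|---|---|---|
| any | any | 0 | 1 + 0 | 1.00 |
| 0.7 | 0.2 | 0.10 | 1 + 0.286 × 0.10 | 1.03 |
| 0.8 | 0.1 | 0.25 | 1 + 0.125 × 0.25 | 1.03 |
| 0.7 | 0.2 | 0.25 | 1 + 0.286 × 0.25 | 1.07 |
| 0.5 | 0.3 | 0.25 | 1 + 0.6 × 0.25 | 1.15 |
| 0.5 | 0.3 | 0.50 | 1 + 0.6 × 0.50 | 1.30 |
| 0.4 | 0.4 | 0.50 | 1 + 1.0 × 0.50 | 1.50 |
| 0.3 | 0.5 | 0.50 | 1 + 1.667 × 0.50 | 1.83 |
| 0.5 | 0.3 | −0.25 | 1 − 0.6 × 0.25 | 0.85 |

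**Simulation check.** The design had 21 clusters of 28 and ICC 0.03 (both within the ranges in SAP Section 2), 4000 runs, pc 0.5, pp 0.3 and a true complier effect of 0.40. The Monte Carlo standard error was about 0.0035.

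| dp | Formula | Simulated |
|---|---|---|
| 0 | 0.40 | 0.397 |
| 0.10 | 0.46 | 0.463 |
| 0.20 | 0.52 | 0.518 |

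**Any use as compliance.** With dp = 0.20, ITT = 0.5 × 0.40 + 0.3 × 0.20 = 0.26. Dividing by the share of users gives 0.26 / 0.8 = 0.325 (simulated 0.324), which is the true average effect among all users. Dividing by the share with 30 or more gives 0.26 / 0.5 = 0.52, against a true 0.40.

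**Count outcomes.** The factor does not transfer to a log link. Assume equal baseline rates, pc 0.5 and a complier rate ratio of 0.70.

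- No partial effect: ITT rate ratio = 0.5 × 0.70 + 0.5 = 0.85. Substituting predicted compliance gives 0.85^(1/0.5) = 0.72, not 0.70. The method is off even when the exclusion restriction holds.
- 30% partial users at rate ratio 0.85: ITT rate ratio = 0.35 + 0.255 + 0.20 = 0.805, and 0.805^2 = 0.65.

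**The case against.** **Benefit below 30 modules is not in the SAP.** This stands. Section 1 says only that completion and dosage vary. A reader might infer that the CACE is certainly inflated, and in a known direction. The document does not support that: the bias is zero if fewer than 30 modules does nothing or if nobody falls in that range, and it reverses if partial use has the opposite effect. What remains is that the SAP claims a property that depends on an assumption it does not mention.

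**The size may be trivial.** This also stands as a possibility. With high completion and a small partial effect the factor is about 1.03, so no single figure should be quoted.

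**The formula may not match the planned model.** Section 6 names no time term for Stage 2, although it includes repeated measures. Read literally on balanced T0 and T1 data, the coefficient would average a null baseline difference with the T1 difference and give about half the T1 ratio. A factor of 1.3 would then become about 0.65. This is a separate gap in the specification. It limits the factor to a linear model that isolates T1, but it does not make the 30-module cut satisfy the exclusion restriction.

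**Any use is not a clean replacement.** Correct. It changes the estimand to the average effect among all users and does not recover the effect of 30 modules. Its own exclusion restriction is more plausible but not guaranteed, because Section 2 embeds the intervention in routine preschool parenting support and families with no modules could be reached indirectly. This argues for adding the analysis, not for substituting it.

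**The analysis is supplementary.** Correct. Section 1 makes ITT primary, and nothing in the SAP makes the CACE a headline result or equates 30 modules with the whole programme.

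**Conclusion.** The concern holds in conditional form. The description as unbiased is not correct in general; it needs exactly zero effect from 1–29 modules on every outcome. The SAP neither states nor defends this, and it is an unlikely condition for a modular programme whose exposure the SAP itself treats as graded.

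If partial users benefit, a linear T1 complier effect is overstated by 1 + (pp/pc)(dp/dc). Under the assumed inputs this is 1.03–1.15 with a small partial effect or few partial users, and 1.3–1.8 with many partial users at half effect. The result rests on one-sided non-compliance up to T1, no effect at zero modules and a Stage 2 model that isolates the T1 contrast. It does not apply directly to the Poisson or negative binomial models, which include caregiver-perpetrated violence. The primary ITT analysis is untouched. The change is worth making, but the trial's main result does not depend on it.

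**What to change.** In SAP Section 6:

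1. Keep the 30-module CACE and state its exclusion restriction: assignment affects outcomes only by bringing participants to 30 or more modules.
2. Replace the unconditional claim with wording such as: unbiased only if completing fewer than 30 modules has no effect. Report the estimate as likely overstated in magnitude if partial users benefit.
3. Pre-specify an additional CACE with compliance defined as at least one module, described as the average effect among all users.
4. Optionally, add an instrumental-variable analysis with number of modules completed as the exposure, and state its linearity assumption.
5. Report the shares with 0, 1–29 and 30 or more modules, so that readers can apply the factor to the linear outcomes themselves.

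These definitions should be fixed before completion data are seen, so that the choice of cut cannot look driven by results.

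**Cost.** The module logs are already needed for the 30-module rule, so the cost is SAP wording and slightly more analysis. The downside is a second complier estimate that is likely smaller and answers a different question, which the report will have to explain.

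### Section 6 ties the two CACE stages to no common sample or timepoint, so the claim of an unbiased complier effect is not secured

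*SAP*

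**What the plan says.** Section 6 of the SAP sets out a two-stage instrumental variable analysis. A complier is a participant who meets a module threshold, "defined as completing at least 30 chatbot modules". In Stage 1, compliance status "will be regressed on the randomization variable to generate predicted compliance probabilities for each participant". Randomisation is the only regressor named. In Stage 2, "Each outcome will be modelled as a function of the predicted compliance indicator from Stage 1", using mixed models with "random intercepts at both the cluster and participant levels to account for data clustering and repeated measures". Linear models serve continuous outcomes, and Poisson or negative binomial models serve counts. Section 6 concludes that the framework "is designed to provide an unbiased estimate of the causal effect of the intervention among compliers".

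Three other places bear on this. Section 3 puts the primary evaluation at T1. Section 5 rules out comparing the arms at T2 and T3, because controls start the intervention after T1. Section 1 applies ITT to the primary analyses but does not say how missing outcomes are handled.

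Section 6 does not name the set on which Stage 1 is fitted, the set or timepoint for Stage 2, a time term, or a rule for missing T1 outcomes.

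**The concern.** With randomisation as the only regressor, the Stage 1 prediction in the intervention arm is a single number: the compliance rate in whatever sample Stage 1 is fitted on. Module completion does not depend on an outcome visit, so it can be known for people who are never assessed at T1. T1 outcomes exist only for those assessed. Because the predictions are saved and passed to a separate mixed model, no software step forces the two stages onto the same records, as a single instrumental-variable routine would.

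If caregivers who finish the modules are also easier to assess at T1, the arm difference at T1 reflects the higher compliance of the assessed group but is divided by the lower compliance of the whole arm. The complier effect is then too large, in the direction that favours the intervention. This concerns the CACE denominator and would remain even if the ITT estimate among those assessed were accepted as it stands.

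**Working it through.** **Inputs.** The structure comes from SAP Section 6, and the restriction to T1 from Sections 3 and 5. The SAP states no compliance rate, retention rate or CACE value, so there is no figure to reproduce and every rate below is an assumption.

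**Notation.** Let p be compliance among all assigned to the intervention, and rC and rN the T1 retention of compliers and non-compliers. Controls have no access before T1, so their predicted compliance is 0.

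**Step 1: compliance among the assessed.** q = p·rC / (p·rC + (1 − p)·rN).

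**Step 2: the linear T1 contrast.** If would-be compliers in the control arm are retained like those in the intervention arm, or if untreated outcomes do not differ by type, the arm difference among the assessed is q × CACE. Stage 2 divides it by the Stage 1 rate. With Stage 1 on everyone assigned the result is (q/p) × CACE, where q/p = rC / (p·rC + (1 − p)·rN). With Stage 1 on the assessed it is CACE.

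| p | rC | rN | q | q/p | Estimate if true CACE is 0.40 SD |
|---|---|---|---|---|---|
| 0.5 | 0.90 | 0.80 | 0.529 | 1.06 | 0.42 |
| 0.7 | 0.90 | 0.70 | 0.750 | 1.07 | 0.43 |
| 0.5 | 0.90 | 0.70 | 0.5625 | 1.125 | 0.45 |
| 0.5 | 0.90 | 0.60 | 0.600 | 1.20 | 0.48 |
| 0.5 | 0.95 | 0.60 | 0.613 | 1.23 | 0.49 |
| 0.3 | 0.95 | 0.70 | 0.368 | 1.23 | 0.49 |
| 0.5 | 0.80 | 0.80 | 0.500 | 1.00 | 0.40 |
| 0.5 | 0.70 | 0.80 | 0.467 | 0.93 | 0.37 |

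Wider retention gaps give more: 0.95 against 0.50 at p = 0.5 gives 0.95/0.725 = 1.31.

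**Step 3: does keeping everyone's T0 row help?** A large simulation was run (4 million participants, no clustering, within-person correlation 0.53, T0 seen for all, p = 0.5, retention 0.90 and 0.60, true CACE 0.40). With Stage 1 on everyone, the T1-only contrast and the random-intercept estimate with a time interaction both gave about 0.48. With Stage 1 on the assessed, both gave about 0.40. Retaining T0 rows does not remove the mismatch.

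**Step 4: dropout by type in the intervention arm only.** Let d be the complier minus non-complier difference in untreated outcome (level for a T1-only analysis, change for a change analysis). The contrast becomes q × CACE + (q − p) × d. At p = 0.5, 0.90/0.70 and CACE 0.40, it is 0.225 + 0.0625d.
- Stage 1 on everyone (divide by 0.50): 0.45 + 0.125d.
- Stage 1 on the assessed (divide by 0.5625): 0.40 + 0.111d.

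The two are equally far from 0.40 when 0.05 + 0.125d = −0.111d, that is d ≈ −0.21. At d = −0.3 the estimates are 0.41 and 0.37.

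**Step 5: Stage 2 taken literally.** With T0 and T1 rows pooled, no time term, no dropout and balanced baselines, the arm difference averages (0 + 0.5 × 0.40)/2 = 0.10, and 0.10/0.5 = 0.20. With dropout the simulation gave about 0.16 to 0.20. All lie well below 0.40.

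**The case against.** The strongest objection is that the mismatch is inferred. The SAP attaches its wording to the prediction, not to the fitting set, and never says that Stage 2 uses fewer people. A reader might infer that the plan fixes Stage 1 on all assigned. It does not: one common analysis set is also compatible with the text. This stands. What can be said is that fitting on everyone is the natural reading and that nothing in Section 6 prevents it.

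A reader might also infer that the CACE is biased away from zero. The document does not support that without conditions. The direction depends on who is retained, and Stage 2 as literally written pulls the estimate towards zero (Step 5). Inflation appears only once Stage 2 is tied to T1, which Sections 3 and 5 in effect require. Curing one fault does not cure the other.

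Nor is it a general rule that both stages must use the same records. Two-sample instrumental-variable estimation is valid when both samples represent the same population. The difficulty here is that dropout related to compliance can break that condition.

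Matching the samples is not a complete remedy either. If only intervention-arm dropout depends on compliance type, a selection term of either sign remains. Step 4 shows that the shared-sample estimate can then be further from the truth, when compliers' untreated outcome runs clearly against the effect (d below about −0.2 in that example). The SAP says nothing about d. This limits the fix but does not justify leaving the samples unspecified.

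Finally, division by a compliance rate does not give the complier effect under a log link, so the argument does not reach the count outcomes, which include caregiver-perpetrated violence. CACE also supplements the ITT analysis. Both points stand.

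**Conclusion.** The concern holds in a conditional form. Section 6 leaves the sample for both stages and the timepoint for Stage 2 open, so its claim of unbiasedness is not secured. For linear outcomes, with Stage 2 read as a T1 contrast and Stage 1 fitted on all assigned, the CACE is multiplied by q/p. Across the assumed rates tabulated this is +6% to +23% where compliers are retained better (by 10 to 35 points), nil where retention is equal, and −7% in the example where they are retained worse. The actual size cannot be fixed from the SAP.

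The multiplier alone describes the bias only if retention by compliance type is alike in the two arms, or untreated outcomes are alike in the two types. The ITT primary analysis is untouched. The point merits a change to the SAP because a better specification is available at almost no cost, and the plausible error, better retention of compliers, would favour the intervention.

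**What to change.** In Section 6:

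- State that Stage 2 estimates the between-group effect at T1, as change from T0 to T1, with no T2 or T3 rows. This has to come first, because the pooled model without a time term has its own bias towards zero.
- For each outcome, fit Stage 1 on the participants with an observed T1 outcome, the same participants who supply the Stage 2 contrast. If imputation or weights are used for missing outcomes, apply the same data sets or weights to both stages.
- Report compliance in the assigned and in the assessed sample side by side.
- Make the unbiasedness claim conditional. Say that the shared sample removes the denominator mismatch but not selection bias if dropout depends on compliance type differently by arm, and add a sensitivity analysis for compliance-related dropout.
- Note that the scaling argument does not carry over to the Poisson and negative binomial outcomes.

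The cost is a few sentences, one Stage 1 fit per outcome and one sensitivity analysis. The downside is a slightly smaller Stage 1 sample and possibly a less favourable CACE.
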